## 6.3 Analytical Specificity

For the evaluation of possible interfering substances for the assay performance different sera (malaria positive, lipaemic, hemolytic sera, see Table 1) will be spiked with ca.10,000 ge copies/mL 17D YF standard preparation. Tests should be performed in triplicate.

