## 2.2 Specific Objectives:

The specific objectives of the evaluation are to:

- Assess the precision of selected technologies
- Verify claims of limit of detection
- Assess interference and potential for cross-reactions
- Assess detection of different wild type YFV strains from Africa and South America
- Assess relative clinical performance using spiked and unspiked specimens collected during non-outbreak times from the clinical setting where the assay is intended to of used.
- Evaluate the operational characteristics of selected technologies, e.g. ease of performance, specimen type utility
- Report and disseminate the findings of the evaluation.

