## 4.3 Analytical Specificity

- Reactivity with other flaviviruses
- Reactivity with other pathogens likely to be encountered in regions with YF.
- Reactivity with potentially interfering or inhibiting endogenous substances

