## 5.4 Analytical Performance Specimen Reference Panel

Reference Panel preparation consists of cell culture-grown YF strains (17D YF vaccine strain, prototype African wild type strain, prototype South American wild type strain) diluted in YF negative serum.

The YF 17D standard preparation (RKI / European Virus Archive (EVA), <https://www.european-virus-archive.com/node/2495>) could be used as 17D reference material. Also the EQA YF Virus 195 panel from QCMD could be used as reference material. This panel comprises YFV 17D in different concentrations, Japanese encephalitis, West Nile, Zika, and Dengue 2 viruses for analysing the assay specificity.

- Precision of measurement:
- Three specimens representing the most relevant YFV strains (17D YFV vaccine strain, African wild type strain, South American wild type strain) will be used. Each YFV-positive specimen will be diluted in serum which has been tested negative for HIV, HBV and HCV to obtain a concentration of ca. 5000 ge copies / mL of the assay.
- Inclusivity:
- Specimens to demonstrate appropriate YF strain detection. They should comprise at least the 17D YFV vaccine strain, an African wild type strain and, a South American wild type strain. These specimens will be diluted to a concentration of 5000 ge copies/mL of the assay.
- Assessment of the Analytical sensitivity:
- The YFV 17D standard preparation from RKI will be used to prepare five-fold serial dilutions in YFV-negative serum comprising at least two concentrations at 5000 ge copies /mL, one concentration at 1000 ge copies /mL and two concentrations at 500 and 100 ge copies/ mL (Tab. 1)
- Analytical Specificity
- Non-YFV flavivirus strains and other pathogens (except malaria). Testing will be conducted with cell culture preparations of the various viruses (using prototype strains) spiked into negative serum specimens. Each virus will be spiked at concentrations found in clinical presentations.
- Interfering substances.
- Testing will be conducted with YFV 17D standard preparation at a concentration of ca. 10^3^ ge copies/mL spiked with challenging sera (see Table 1) in order to detect potential interference for the assays under evaluation. The malaria specimens will be those identified as positive by microscopy.

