### Table 1: Assay Performance Specimen Reference Panel

| **Analyte - Sample type** | **Concentration (copies/mL)** | **N° of replicates** | **Total N° replicates** |
| --- | --- | --- | --- |
| **Precision of measurement and inclusivity** |  |  |  |
| **Intra-assay precision/inclusivity** |  |  |  |
| YF 17D vaccine strain* | Each strain will be diluted at a concentration of ca. 10^3^, 10^4^ and 10^5^ ge copies /mL and run in quadruplicate | 3 | 12 |
| African wild type strain* |  | 3 | 12 |
| South American wild type strain* |  | 3 | 12 |
| **Inter-assay precision** |  |  |  |
| YF 17D vaccine strain* | Each strain will be diluted at a concentration of ca. 10^3^, 10^4^ and 10^5^ ge copies /mL and run in quadruplicate on 3 different days by different technicians (day 1 can use intra-assay data) | 3 | 24 |
| African wild type strain* |  | 3 | 24 |
| South American wild type strain* |  | 3 | 24 |
| **Inter-lot variability** |  |  |  |
| YFV 17D vaccine strain* | Each strain will be diluted at a concentration of ca. 10^3^, 10^4^ and 10^5^ and run in quadruplicate | 3 | 12 |
| YFV African wild type strain* |  | 3 | 12 |
| YFV South American wild type strain* |  | 3 | 12 |
| **Analytical Sensitivity** | | | |
| YFV Standard preparation* | ca. 10, 50, 100, 500, 1000, 5000, 10^4^, 5x10^4^, 10^5^, 5x10^5^, 10^6^ , 5x10^6^ ge copies /mL** | 5 | 25 |
| **Analytical Specificity (**Flavivirus strain detection) | | | |
| Hepatitis C* virus | Medium concentration  ca. 10,000 ge copies/mL | 1 |  |
| Dengue 1, 2, 3, 4*virus |  | 1 |  |
| Zika virus* |  | 1 |  |
| West Nile virus* |  | 1 | 9 |
| Tick Borne Encephalitis virus* |  | 1 |  |
| Japanese Encephalitis virus* |  | 1 |  |
| **Analytical Specificity (other pathogens)** | | | |
| Ebola virus* | medium concentration  ca. 10,000 ge copies/mL | 1 |  |
| Lassa fever virus* |  | 1 |  |
| Marburg virus* |  | 1 |  |
| HIV* |  | 1 | 8 |
| Hepatitis E virus* |  | 1 |  |
| Chikungunya virus* |  | 1 |  |
| Measles virus* |  | 1 |  |
| Influenza virus* |  | 1 |  |
| **Analytical Specificity (interfering substances)** | | | |
| Haemoglobin | 200 g/L | 3 |  |
| Triglyceride | 5.6 mmol/L | 3 | 12 |
| Bilirubin (unconjugated) | 257 µMol/L | 3 |  |
| Malaria positive sera |  | 3 |  |
| **Clinical Performance Panel** | | | |
| Non-reactive serum specimens Spiked African wild type | 5000 ge copies/ mL | 10 | 10 |
| Non-reactive serum specimens Spiked South American wildtype | 5000 ge copies/ mL | 10 | 10 |

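### The designated malaria sera are tested only with YFV 17D present, so they can show inhibition but not a false positive caused by malaria

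*Protocol*

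**What the plan says.** Among the specific objectives, section 2.2 lists: "Assess interference and potential for cross-reactions". Section 4.3 separates the two readings. One of its items is "Reactivity with other pathogens likely to be encountered in regions with YF", and another covers endogenous substances that might interfere with or inhibit the assay.

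Malaria then appears in three places:

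- Section 5.4 introduces the cross-reactivity material as "Non-YFV flavivirus strains and other pathogens (except malaria", and describes cell-culture virus preparations added to negative serum. Under interfering substances it says that the 17D standard is "spiked with challenging sera (see Table 1) in order to detect potential interference for the assays under evaluation", and adds: "The malaria specimens will be those identified as positive by microscopy".
- Section 6.3 says that "different sera (malaria positive, lipaemic, hemolytic sera, see Table 1) will be spiked with" the 17D standard at ca. 10,000 ge copies/mL, with tests in triplicate.
- Table 1 has one line, "Malaria positive sera", with 3 replicates in the interfering-substances block. Malaria is not among the eight entries under other pathogens.

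No section plans a specimen that is known to contain malaria and is free of YFV.

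**The concern.** Cross-reaction and interference need opposite specimens. Cross-reaction is read from a specimen that contains the other pathogen and no YFV, where the right answer is negative. Interference is read from a specimen that contains YFV, where the right answer is positive. Malaria gets only the second kind.

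The block sits under the analytical specificity heading in Table 1, and section 8.3 asks for each analyte to be reported separately. The report would thus carry a malaria line under specificity with no false-positive information behind it. Malaria is the only pathogen in Table 1 in that position.

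**Working it through.** **1. Reproduce the plan's count.** The interference block in Table 1 has four substances (haemoglobin, triglyceride, bilirubin, malaria) with 3 replicates each: 4 × 3 = 12, which matches the stated 12. Three of these are malaria tests. All are spiked, so the number of unspiked designated malaria tests is 0.

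**2. Compare with the other pathogens.** The flavivirus block has 9 tests: hepatitis C, dengue 1 to 4, Zika, West Nile, tick-borne encephalitis and Japanese encephalitis. The other-pathogens block has 8. All 9 + 8 = 17 are single tests in negative serum, so each can show a false positive.

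**3. What a spiked malaria serum can show.** Let d be the probability that the 17D spike is detected and f the probability that malaria alone produces a signal. The protocol gives neither, so both are assumed, and they are taken as independent:

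P(positive) = 1 − (1 − d)(1 − f)

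| d | f = 0 | f = 0.1 | f = 0.5 | f = 1 |
|---|---|---|---|---|
| 1.00 | 1.000 | 1.000 | 1.000 | 1.000 |
| 0.99 | 0.990 | 0.991 | 0.995 | 1.000 |
| 0.95 | 0.950 | 0.955 | 0.975 | 1.000 |

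The row d = 0.95 is an assay that only just meets the section 8.3 limit (95% detection at 1000 ge copies/mL), tested at the 10^3 spike of section 5.4. Even there, the chance of three positives out of three moves from 0.95³ = 0.857 at f = 0 to 0.975³ = 0.927 at f = 0.5. Cross-reaction makes the expected result more likely, so no outcome of the three tests points to it. It can also hide inhibition: if the spike were fully suppressed (d = 0), P(positive) = f.

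**4. What three unspiked malaria tests would show.** The chance of at least one false positive is 1 − (1 − f)³:

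- f = 0.1: 1 − 0.9³ = 27.1%
- f = 0.2: 1 − 0.8³ = 48.8%
- f = 0.5: 1 − 0.5³ = 87.5%
- f = 1: 100%

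With 0 of 3 positive, the exact two-sided 95% upper limit is 1 − 0.025^(1/3) = 70.8%. For comparison, 0/10, 0/20 and 0/30 give 30.8%, 16.8% and 11.6%.

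**5. What the 80 unspiked clinical negatives contribute.** With an assumed malaria prevalence m among them, the chance of at least one malaria-related false positive is 1 − (1 − m·f)^80. At f = 0.1:

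- m = 0: 0
- m = 0.05: 1 − 0.995^80 = 33.0%
- m = 0.10: 1 − 0.99^80 = 55.2%
- m = 0.30: 1 − 0.97^80 = 91.3%

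The result depends entirely on m, which the protocol neither fixes nor measures.

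**The case against.** The strongest reply is that the evaluation as a whole is not blind to malaria. Section 5.1 takes the clinical sera from an endemic setting and, where possible, from patients with symptoms like those of YF. Section 6.4 requires 100% agreement for negatives, so a single false positive in an incidental malaria specimen would breach the criterion. This stands. A reader might infer that a malaria-related false positive could not be seen anywhere, and the protocol does not support that. What remains is attribution: without malaria status, 80 of 80 negative does not show that malaria was tested, and a positive could not be traced to it.

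Three other strong readings also go beyond the text:

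- *That section 5.4 deliberately drops malaria from cross-reactivity testing.* The parenthesis may mean only that malaria is not a cell-culture virus preparation. On either reading, Table 1 and section 6.3 still provide no unspiked malaria specimen.
- *That a cross-reacting malaria serum would be scored as a pass.* No pass rule is set for the interference panel. Section 8.3 asks only for separate reporting and a note of unexpected results.
- *That the protocol contradicts its objectives.* Sections 2.2 and 4.3 do not name malaria, section 4 calls the evaluation risk-based, and section 1.2 says that it does not replace the manufacturer's validation. Treating malaria as an interferent is a design choice, and the gap is one of coverage.

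It is also fair to say that three unspiked tests are weak. They find gross cross-reaction and cannot bound a low rate. However, the protocol accepts a single test for each of the 17 viruses, so three is above its own standard.

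**Conclusion.** The point holds for the specimens that the protocol designates as malaria-positive. All of them carry YFV 17D, so 0 of 3 can show a false positive caused by malaria, whatever the true rate. For malaria, the cross-reaction aim of sections 2.2 and 4.3 is not met by its designated specimens, whereas for the 17 viruses it is.

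The count comes from the text alone. The probabilities rest on assumed values of d, f and m and on independence of the two signals, and the conclusion does not depend on which values are chosen. A Ct shift in a spiked serum might hint at non-specific signal, but no Ct criterion is set for this test, and a shift would not demonstrate a false positive.

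This is a cheap improvement. The evaluation remains valid without it, but a statement about malaria cross-reactivity would have no designated specimen behind it.

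**What to change.** - In section 6.3 and Table 1, also run the microscopy-positive malaria material unspiked, in three tests with an expected negative result, reported under cross-reactivity. Keep the spiked runs and report them under interference.
- State whether the 3 in Table 1 means three different sera or one serum in triplicate. The wording allows both, and three different sera say more about cross-reaction.
- Reword the malaria exception in section 5.4 to say that malaria is represented by patient sera instead of culture preparations.
- In the report, state that the unspiked arm detects only gross cross-reaction, with the 70.8% upper limit for 0/3.
- While editing, reconcile the 17D spike for this panel, which is ca. 10^3 ge copies/mL in section 5.4 and ca. 10,000 in section 6.3.

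Cost: about three more tests per assay. The Table 1 rows sum to 36 + 72 + 36 + 25 + 9 + 8 + 12 + 100 = 298 and would become 301. The printed totals (305 in Table 1, 310 in section 10) need restating in any case. The protocol does not say how much malaria material is available, so the added arm depends on specimen volume.

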## 6.5 Interpretation and recording of test results

The interpretation of results for each assay under evaluation is made according to the manufacturer’s instructions. All runs and/or test results are recorded on a data sheet.
Preferably all test results are recorded and exported directly from the instrument to standardized test result worksheets for further data analysis.

A technician's analysis is made of each assay under evaluation and is completed by the operator performing the testing. This analysis comprises operational characteristics, ease of the procedure, reading and interpretation of results, clarity of manufactural instructions, as well as records of any specific difficulties encountered during the evaluation. Special attention should be paid to the instruction leaflet regarding clarity, presentation, content and safety issues in order to evaluate whether these instructions are sufficient for diagnostic laboratories in developing countries.

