## 7.2 External quality control specimen

The evaluating site will run a validated external control specimen. This external quality might be available from a commercial source (EVA, QCMD, see above). The 17D standard preparation in a medium (10,000 ge copies/mL) and low (1,000 ge copies/mL) concentration spiked in a YF negative test human serum should be used.

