## 8.3 Analytical Sensitivity and Specificity

The limit of detection (LoD) is the lowest concentration of analyte that can be consistently detected in at least 95% of specimens tested under routine laboratory conditions and in a given specimen matrix. It defines the analytical sensitivity. The sensitivity and LoD will be estimated using the Probit analysis on the results of the five replicates of the LoD panel.

An acceptance criteria for the lower performance limit of the assay shall be ≤1000 ge copies/mL. Assays that do not reach this LoD will not be considered for listing by the WHO.

The results of testing for each individual analyte should be reported separately. Where unexpected results have been encountered, these should be noted in the report

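### The interference experiment names no interferent-free comparator and no Ct-shift readout; read as detected or not detected at 10,000 ge/mL, it would usually pass an assay that loses about 90% of its template

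*Protocol*

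**What the plan says.** Assessing interference is one of the specific objectives (Protocol 2.2), and 4.3 extends it to inhibiting substances. The experiment is described in three places.

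- Section 5.4: "Testing will be conducted with YFV 17D standard preparation at a concentration of ca. 10^3^ ge copies/mL spiked with challenging sera", with the purpose "in order to detect potential interference for the assays under evaluation".
- Section 6.3: the sera "will be spiked with ca.10,000 ge copies/mL 17D YF standard preparation. Tests should be performed in triplicate".
- Table 1: four interferents (haemoglobin, triglyceride, bilirubin, malaria-positive sera) with three replicates each. The block total stands in the triglyceride row: "Triglyceride | 5.6 mmol/L | 3 | 12". The block has no row for 17D without an interferent.

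On reading the results, 6.5 says "The interpretation of results for each assay under evaluation is made according to the manufacturer’s instructions", and 7.5 says the same. In the analysis section, 8.3 adds "The results of testing for each individual analyte should be reported separately" and asks that unexpected results be noted. Neither section mentions a comparison or a limit for interference.

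A suitable comparator is already run for another purpose. The external control in 7.2 is "The 17D standard preparation in a medium (10,000 ge copies/mL) and low (1,000 ge copies/mL) concentration spiked in a YF negative test human serum".

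**The concern.** Inhibition is a loss of signal relative to the same input without the inhibitor. A detected call on a spiked serum shows only that the loss was not complete. How much loss can hide behind three detected calls depends on how far the spike lies above the assay's LoD. At the level in 6.3 the spike is ten times the LoD acceptance limit, so the margin is wide even for the least sensitive assay that could be listed. A report of no interference could then cover a large loss of template, which would matter for patient sera with low viral load. At the level in 5.4 an assay near the acceptance limit has the opposite problem: a chance miss can look like interference, and there is no clean-serum result beside it to tell the two apart.

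**Working it through.** **Inputs from the Protocol.** Spike 10,000 ge/mL (6.3) or 10^3 ge/mL (5.4); 3 replicates and 4 interferents (Table 1); LoD defined by 95% detection, acceptance limit 1000 ge/mL (8.3).

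**Assumptions.** Results are read as detected or not detected. Detection follows a single-hit curve set to 95% at the LoD. PCR efficiency is 100%, so Ct shift = log2(1/remaining fraction). The Ct SD is not in the Protocol; 0.3 to 0.7 is used as a range.

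**Table 1 block total.** 4 × 3 = 12, as stated. All 12 tests contain an interferent.

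**Chance of 3/3 detected.** With remaining concentration c = spike × (1 − loss), p = 1 − exp(−ln 20 × c/LoD) and P(3/3) = p³. Example: spike 10,000, LoD 1000, 90% loss gives c = 1000, p = 0.95 and P = 0.95³ = 0.86.

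| Spike | LoD | No loss | 50% | 75% | 87.5% | 90% |
|---|---|---|---|---|---|---|
| 10,000 | 500 | 1.00 | 1.00 | 1.00 | 0.998 | 0.99 |
| 10,000 | 1000 | 1.00 | 1.00 | 0.998 | 0.93 | 0.86 |
| 1000 | 500 | 0.99 | 0.86 | 0.47 | 0.15 | 0.09 |
| 1000 | 1000 | 0.86 | 0.47 | 0.15 | 0.03 | 0.02 |

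At 10,000 ge/mL, a probit curve with SD 0.3 log10 gives nearly the same values for LoD 1000 (0.93 at 87.5% loss, 0.86 at 90%). At 10^3 ge/mL and LoD 1000 it gives 0.40 instead of 0.47 at 50% loss.

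**Chance misses.** At spike 10^3 and LoD 1000 with no interference, at least one of the four interferents shows a miss with probability 1 − 0.857^4 = 0.46. At 10,000 ge/mL this is essentially zero.

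**What three detections prove.** The exact two-sided 95% lower limit for the detection rate after 3/3 is 0.025^(1/3) = 0.29.

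**The only Ct tolerance in the Protocol.** The 3 Ct in 6.2 belongs to precision. Borrowed for interference, it would pass a loss of up to 1 − 2^(−3) = 87.5%.

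**What a Ct comparison would add.** With 3 interferent and 4 clean replicates, SE = SD × √(1/3 + 1/4) = 0.764 × SD on 5 df. The 95% half-width is 2.571 × SE.

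| Within-run SD (Ct) | 95% half-width (Ct) | Power, 50% loss (1 Ct): one-sided 5% | Power, 50% loss: 95% CI excludes 0 | Power, 80% loss (2.3 Ct): one-sided 5% |
|---|---|---|---|---|
| 0.3 | 0.59 | 0.98 | 0.93 | about 1.00 |
| 0.5 | 0.98 | 0.73 | 0.56 | about 1.00 |
| 0.7 | 1.37 | 0.49 | 0.33 | 0.98 |

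For 90% loss (3.3 Ct) the one-sided power is about 1.00 throughout. With four interferents against one clean arm and no true effect, the one-sided 5% test flags at least one in about 15% of assays, and a 95% CI lying wholly above zero does so in about 8%.

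**The case against.** A reader might infer that the Protocol reads interference only as positive or negative. It does not say so. It names no readout, 6.5 prefers direct instrument export, and 6.2 already works in Ct for precision. The figures for calls are therefore conditional on that reading.

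A reader might also infer that clean-serum 17D is missing or is never to be compared. That is too strong as well. 17D in negative serum at both candidate levels is the external control (7.2), and a failed control invalidates the run (7.4). What is missing is a stated comparison, not the material.

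Nor does the risk of hidden loss hold at every spike level. At 10^3 ge/mL the call shows 80% loss fairly often: P(3/3) is 0.34 at LoD 500 and 0.09 at LoD 1000. The 46% chance-miss figure needs that spike level and an LoD exactly at the limit. Even then 8.3 asks only that unexpected results be noted, not that they be called interference.

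Further points stand in part. Internal controls (7.1) may flag strong inhibition where a kit has them, but no interference rule uses them. The evaluation does not replace the manufacturer's validation (1.2). The choice of contrast and interval could sit in an analysis plan that is not shown. However, sharing the run, stock and spike level is a design matter to be settled before testing, and section 8 of this Protocol is where the analysis of this block is laid down.

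**Conclusion.** The point holds in a limited form. The Protocol sets neither a comparator nor a Ct-shift readout for interference, although nearly everything needed is already in the plan. Followed as written and read by calls at 10,000 ge/mL, it can report no interference for an assay at the LoD limit with probability 0.93 at 87.5% loss and 0.86 at 90% loss, and more often for more sensitive assays. At 10^3 ge/mL the weakness shifts towards unexplained chance misses for assays near the limit. Sections 5.4 and 6.3 contradict each other on the level, so the Protocol does not settle which case applies. The sizes rest on the single-hit curve and a call-only reading. The absence of a comparator does not depend on either.

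**What to change.** 1. Reconcile the spike level between 5.4 and 6.3.
2. In 6.3, test the interferent triplicates in the same run as 3 to 4 replicates of the same 17D standard preparation, at the same level and spike volume, in clean YF-negative serum. This means replicating the 7.2 control. The precision quadruplicate can serve only if it is the same stock and level. That is not established: Table 1 calls it the vaccine strain, and 5.4 puts the precision panel at ca. 5000 ge/mL while Table 1 and 6.2 give 10^3 to 10^5.
3. In 8.3, report for each interferent the mean Ct difference (interferent minus clean) with its 95% CI, next to the detection counts. Count a replicate without a Ct as not detected; do not drop it silently.
4. Judge the difference against a Ct-shift limit fixed before testing, not by significance alone. If the upper confidence limit must fall below it, the limit has to exceed the half-widths above.
5. For assays that give no Ct, report detection in both arms side by side.

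The cost is protocol wording, run layout and up to 3 to 4 extra wells for each run that holds interferent tests. The gain is limited for small effects: a 50% loss is seen reliably only at a within-run SD of about 0.3 Ct, whereas losses of 80 to 90% are seen well across SD 0.3 to 0.7.

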**6.2 Analytical Performance Testing**

The determination of precision and inclusivity will be undertaken in a single set of experiments.

- Four specimens will be used: one YF negative, one YF 17D, one YF African wild type, and one YF South American wild type, at a concentration of 10^3^-10^5^ ge copies /mL, (see Table 1).
- Intra-run variability (repeatability): The same sample panel (ca.10^3^, 10^4^, 10^5^ ge copies/mL) should be tested on the same run. Each panel member should be tested in quadruplicate.
- Inter-run variability (reproducibility): The same sample panel (ca. 1000, 10^4^, 10^5^ ge copies/mL) should be tested in 3 different runs preferably by different technicians.Each panel member should be tested in quadruplicate on each run.
- Inter-lot variability: The same sample panel (ca.10^3^, 10^4^, 10^5^ ge copies/mL) should be tested on a second lot of the product. Tests should be performed in quadruple.

Results should not vary by more than 3 ct values, by frequent performance in the same laboratory.

Twelve concentrationss of YF 17D standard preparation, diluted as described in Table 1, will be tested 5 times. The 5 replicates will be separated in a minimum of three runs where applicable.

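### Sections 5.4 and 6.3 set the YFV level in the same twelve interference tests a factor of 10 apart, and under a positive/negative reading the level affects what the tests can show

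*Protocol*

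**What the plan says.** Protocol section 5.4, under interfering substances: "Testing will be conducted with YFV 17D standard preparation at a concentration of ca. 10^3^ ge copies/mL spiked with challenging sera". Section 6.3, on the same experiment: the challenging sera "will be spiked with ca.10,000 ge copies/mL 17D YF standard preparation", followed by "Tests should be performed in triplicate".

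Both sections point to Table 1. Its interference block has four rows (haemoglobin, triglyceride, bilirubin, malaria-positive sera) with three replicates each and a total of twelve, for example "Triglyceride | 5.6 mmol/L | 3 | 12". The concentration column there holds the level of the interferent. No YFV level is given.

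Section 8.3 defines the LoD as the concentration "consistently detected in at least 95% of specimens tested under routine laboratory conditions" and adds: "An acceptance criteria for the lower performance limit of the assay shall be ≤1000 ge copies/mL". On reading results, section 6.5 says: "The interpretation of results for each assay under evaluation is made according to the" manufacturer's instructions. The only Ct tolerance in the protocol stands under precision in section 6.2: "Results should not vary by more than 3 ct values".

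**The concern.** A laboratory that follows 5.4 and one that follows 6.3 both comply with the protocol, yet they run different experiments. The spike level is a bench setting that the protocol fixes twice, so it cannot be left to a later analysis plan.

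Assessing interference is one of the specific objectives in section 2.2. If the result is read only as detected or not detected, the distance between the spike and the assay's LoD determines how much template an interferent can remove before a replicate turns negative. At ten times the highest accepted LoD, that distance is large. Results for two assays tested at different levels would also not be comparable.

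**Working it through.** **The protocol's own count.** 4 substances × 3 replicates = 12, which agrees with Table 1. The protocol states no detectable loss for this experiment, so there is no further figure to reproduce.

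**Inputs.** Spike about 10^3 (5.4) or about 10,000 ge copies/mL (6.3). Three replicates (6.3, Table 1). LoD defined at 95% detection and at most 1000 ge copies/mL (8.3). Assumed: 90% loss of template, with 95% and 99% as variants, and independent replicates.

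**At 10,000.** A 90% loss leaves 10,000 × 0.1 = 1,000 ge copies/mL, the highest LoD that the protocol accepts. Each replicate is still detected with probability at least 0.95, so P(3/3 positive) ≥ 0.95^3 = 0.857. This needs no assumption about the shape of the detection curve.

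**At 10^3.** The same loss leaves 100 ge copies/mL. For most assays this lies below the LoD, so a curve is needed. The single-hit form fixed at 95% at the LoD is p = 1 − 0.05^(c/LoD), where c is the concentration left.

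| LoD | From 10,000: p, p^3 | From 10^3: p, p^3 |
|---|---|---|
| 1000 | 0.950, 0.857 | 0.259, 0.017 |
| 500 | 0.9975, 0.993 | 0.451, 0.092 |
| 300 | >0.999, >0.999 | 0.632, 0.252 |
| 100 | >0.999, >0.999 | 0.950, 0.857 |

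A probit curve on log10 concentration, with assumed SD 0.3 and 0.5, gives 0–5% for the 10^3 column at LoD 1000, 2–21% at LoD 500 and 14–43% at LoD 300.

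**Larger losses at 10,000, LoD 1000 (single-hit).**
- 95% loss: 500 left, p = 1 − 0.05^0.5 = 0.776, p^3 = 0.47.
- 99% loss: 100 left, p = 0.259, p^3 = 0.017.

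**Chance misses at 10^3 with no interference, LoD exactly 1000.** Per triplicate, 1 − 0.95^3 = 0.143. Over twelve tests, 1 − 0.95^12 = 0.46.

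**Ct shift from a 90% loss.** ΔCt = log(10)/log(1 + E), where E is the amplification efficiency. This gives 3.32 at E = 1 and 3.59 at E = 0.9, against the 3 Ct in 6.2. At E = 1, a shift of 3 Ct corresponds to a loss of 1 − 2^−3 = 87.5%, so the margin is thin. For the mean of three replicates against the mean of four, SE = SD × √(1/3 + 1/4). With a true shift of 3.32, the observed difference exceeds 3 with probability 92%, 80% and 66% for assumed single-Ct SDs of 0.3, 0.5 and 1.0.

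**The case against.** The best reply is that little depends on this. Section 8.3 ties listing to the LoD and attaches no pass/fail rule to interference; unexpected results are noted in the report. Section 6.5 prefers direct export from the instrument, so Ct values would often be at hand. Section 7.1 describes internal controls, and section 8.2 counts invalid results, so an inhibited reaction may show there. This stands in part. These routes exist, but the protocol does not apply any of them to interference, and none removes the conflict over the level. A separate analysis plan may set a reading rule; it is not at hand.

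Three stronger readings are tempting, and the documents do not support them:

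- **That 10,000 makes a finding of no interference almost certain.** This holds for losses up to about 90%. At LoD 1000, a 95% loss leaves 3/3 positive in only 47% of triplicates and a 99% loss in 1.7%.
- **That 10^3 cures the problem.** It helps on detection when the LoD is near the limit. At LoD 100, a 90% loss from 10^3 is missed in 86% of triplicates. Table 1 offers dilutions down to about 10 ge copies/mL, chosen around the manufacturer's LoD, so sensitive assays are foreseen.
- **That bilirubin was dropped.** The list in 6.3 leaves it out but refers to Table 1, where bilirubin has three replicates.

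A comparator does not by itself resolve a chance miss on detection. With 2/3 positive against 4/4, the Fisher p-value is 3/7 = 0.43. The Ct comparison carries that weight.

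**Conclusion.** The contradiction is real and unresolved in the current text: two YFV levels, a factor of 10 apart, govern the same twelve tests. Under a positive/negative reading, a 90% loss goes unseen at 10,000 in at least 86% of triplicates for any assay that meets the LoD limit. At 10^3 the figure runs from 1.7% (LoD 1000) to 86% (LoD 100).

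The 86% bound at 10,000 rests on the protocol's own LoD definition and on independent replicates. The 90% loss is an assumed scenario, and the figures below the LoD depend on the assumed curve. The documents do not make either level correct in itself. They require that one be chosen and that the reading suit it.

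**What to change.** - State one YFV level for the interference test, in the same words, in 5.4, 6.3 and Table 1.
- Judge interference by detection and by Ct shift against the interferent-free 17D precision quadruplicate at that same level, run on the same plate. Table 1 and section 6.2 already plan this quadruplicate at both 10^3 and 10^4. Make it from the same 17D preparation and in clean serum. Section 5.4 gives about 5000 for the precision specimens, so that figure must agree with Table 1 for the comparator to match.
- Fix the Ct threshold in advance. The 3 Ct in 6.2 is written for precision, and a 90% loss exceeds it only narrowly.
- Weigh the choice of level openly. The 10^3 level is more sensitive on detection for assays with an LoD near 1000. Its price is a chance miss in 14% of triplicates, and in 46% of full sets of twelve, for an assay exactly at the limit. A single miss should therefore not be read as interference without the Ct comparison. The Ct comparison can be made at either level.
- Annex 1 allows for end-point detection. Say how interference is read where an assay yields no Ct.
- Name bilirubin in 6.3, as a minor clarification.

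The cost is protocol wording and plate layout, with no added tests.
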